**Figure 1. F1:**
[figure not shown]
Schematic representation of the planned workflow. Blood samples from patients will be collected at 4 time points. The collected samples will be processed and prepared for further analyses in transcriptomics, epigenetics, and proteomics. Clinical data will be incorporated into the data integration pipeline and processed, so that they can be combined with the results from transcriptomics, epigenetics, and proteomics for the final evaluation in the context of integrative data analysis. AI: artificial intelligence; AUC: area under the curve; cDNA: complementary DNA; ELISA: enzyme-linked immunosorbent assay; ETL: extract, transform, load; EV: extracellular vesicle; FPR: false positive rate; LC-MS/MS: liquid chromatography–tandem mass spectrometry; MACS: magnetic-activated cell sorting; OMOP CDM: Observational Medical Outcomes Partnership Common Data Model; post-OP: postoperative; pre-OP: preoperative; qRT-PCR: quantitative reverse transcription polymerase chain reaction; ROC: receiver operating characteristic.

At study inclusion, each patient’s cognitive status is assessed to ensure eligibility and to document baseline cognitive function. In order to determine whether cognitive disorders are already present, a Mini-Mental State Examination and a Delirium Risk Assessment Score (DRAS) test are included as part of the consent process. The DRAS is determined preoperatively in the preanesthesia clinic by evaluating patient-related factors such as age, comorbidities, type of surgery, and medication use. The individual items are summed up to generate a total score, with higher values indicating an increased risk of POD.

Patients will undergo general anesthesia according to the clinic’s standard protocol, which includes the administration of propofol, sufentanil, and, if required, rocuronium for muscle relaxation, as well as maintenance with sevoflurane. Anesthesia depth is strictly monitored using Narcotrend (Narcotrend-Gruppe) with a target anesthesia depth of stages D0-E2. Delirium is assessed preoperatively, upon transfer from the recovery room, and on the 5 postoperative days using the Confusion Assessment Method (CAM), the CAM for the ICU (CAM-ICU), and the Delirium Observation Scale [15,16].

### Blood Sampling and Analysis

In addition, 20 mL of venous whole blood will be collected in ethylenediaminetetraacetic acid, serum, RNA exact, and DNA exact tubes (Sarstedt) at 4 points in time: during premedication, immediately postoperatively, on the second postoperative day, and on the fifth postoperative day. Serum and plasma samples, proteins, DNA, and RNA will be extracted from these whole blood samples. Furthermore, specific cell fractions such as neutrophils, macrophages, and peripheral blood mononuclear cells will be isolated. Proteins will be isolated from these cell samples and, together with plasma, subjected to the proteomic analysis using mass spectrometry to identify potentially significant proteins. Concurrently, an analysis of candidate genes, such as ACHE, BCHE, CHRNA7, chemokines, and cytokines, will be conducted to investigate methylation processes associated with the occurrence of POD. For methylation analysis, DNA samples are subjected to bisulfite conversion, and methylation will be quantified using quantitative polymerase chain reaction with specific primers [17]. The activity of acetylcholinesterase and butyrylcholinesterase will be assessed using ELISA (enzyme-linked immunosorbent assay).

In addition, an in silico analysis of the identified target genes will be performed to identify potential polymorphisms. Polymorphisms that appear potentially relevant will be genotyped in the entire patient cohort using the TaqMan Assay (TaqMan SNP Genotyping Assays; Thermo Fisher) [18,19]. In the final step, the identified genes and proteins will be quantified together with known inflammatory markers (tumor necrosis factor-α, interleukin-6 [IL-6], and interleukin-10) from serum samples using ELISA or the LegendPlex assay (BioLegend) [20]. The blood plasma obtained during cell isolation will also be used for measuring tumor necrosis factor-α and other cytokines (IL-6, interleukin-10, etc) via ELISA. In addition, neuron-specific enolase and S-100 β protein levels will be determined from the remaining blood preoperatively and 48 hours and 5 days postoperatively. The remaining DNA, RNA, and plasma samples will be stored at −20 °C and −80 °C to ensure the possibility of repeat measurements in case of technical errors. The samples will also be preserved for further validation of significant proteins from the proteomic analysis using ELISA and to investigate their genetic basis (polymorphisms and DNA methylation).

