## Introduction

Delirium is a common postoperative complication, particularly in patients above the age of 65 years, and its causes are still largely unexplored [1]. Nevertheless, the effects of delirium are very serious for patients and, in some cases, can even drastically affect quality of life and even life expectancy. The incidence of postoperative delirium (POD) in older patients is 5% to 10% on average but can be higher in high-risk procedures such as total joint arthroplasty [2]. POD is therefore a frequent and life-threatening complication. At the center of this clinical picture is a functional disorder of the brain. Patients are affected symptomatically by disorientation, restlessness, hallucinations, or anxiety [3]. Despite these impressive and often serious symptoms, POD is often recognized late, and successful intervention is delayed [4]. However, it should be noted that the more time elapses before the diagnosis is made, the higher the probability of a severe and complicated course of POD. POD is associated with prolonged hospital stays, extended ventilation times, increased care requirements, and higher mortality rates [5]. Recovery from POD has considerable intraindividual variability, ranging from hours to months, and can present as a hypoactive, hyperactive, or mixed subtype, characterized by symptoms such as apathy, confusion, agitation, delusions, and signs of sympathetic arousal [6]. The pathophysiology of POD is not yet fully understood, but it is hypothesized to be related to acute disruptions in neurotransmitter levels and neuroinflammation [1]. Risk factors for POD include preoperative impaired cognitive and general health status, frailty, medical comorbidities such as hypotension and hypoxia, and exposure to psychoactive drugs [7]. Postoperative neuroinflammation, which is a major contributor to the development and progression of POD, can be exacerbated by complications such as infections, pulmonary issues, and hypoxemia [8]. The use of certain anesthetics has also been linked to long-term alterations in brain morphology and function, particularly at the extremes of age [9,10]. It is known from previous studies that the plasma levels of neuron-specific enolase and S-100 β protein may correlate with POD [11]. However, there are currently no valid laboratory tests for diagnosis. Furthermore, apart from an avoidance strategy for possible triggering drugs, there are only a few effective preventive and therapeutic approaches [3,12,13]. Existing models rely on clinical variables or single biomarkers. Our study integrates multiomics with advanced machine learning (ML) to explore novel predictive signatures and underlying biological mechanisms.

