### Methodology

After obtaining consent, patients are enrolled in the study. The study workflow for each patient is outlined in Table 1 and illustrated in Figure 1.

**Table 1. T1:** Study timeline detailing the timing of various procedures and data collection points throughout the study for each individual patient.

Time point	Study enrollment	Baseline	Preoperative (induction)	Intraoperative	Postoperative (recovery room)	Day 1	Day 2	Day 3	Day 4	Day 5	Hospital discharge	30-day follow-up	90-day follow-up
Study enrollment													
Screening for inclusion and exclusion criteria	✓												
Informed consent	✓												
Measurements													
Blood collection			✓		✓		✓		✓				
Microarray analysis of whole blood RNA		✓			✓								
Epigenetic analysis of whole blood DNA		✓			✓								
Genotyping of whole blood DNA		✓											
Serum/plasma storage		✓	✓	✓	✓		✓		✓				
ELISA^a^ from serum samples		✓	✓	✓	✓		✓		✓				
Isolation of neutrophils*,* PBMCs^b^, and macrophages		✓	✓	✓	✓		✓		✓				
Proteomic analyses		✓	✓	✓	✓		✓		✓				
AChE^c^ measurement		✓	✓	✓	✓	✓	✓	✓	✓	✓			
Clinical data collection													
Demographic and medical baseline data		✓											
Surgery-specific data				✓									
Complete digital anesthesia documentation			✓	✓	✓								
Intraoperative EEG^d^ monitoring				✓									
All clinical parameters		✓	✓	✓	✓	✓	✓	✓	✓	✓	✓		
Complete progress documentation		✓	✓	✓	✓	✓	✓	✓	✓	✓	✓		
Delirium screening (CAM^e^ or CAM-ICU^f^)			✓	✓	✓	✓	✓	✓	✓	✓	✓		
Neuropsychological status (RBANS^g^)											✓	✓	✓
Health-related quality of life (SF-36^h^)											✓	✓	✓
Mortality											✓	✓	✓

a ELISA: enzyme-linked immunosorbent assay.

b PBMSs: peripheral blood mononuclear cells.

c AChE: acetylcholinesterase.

d EEG: electroencephalogram.

e CAM: Confusion Assessment Method.

f CAM-ICU: Confusion Assessment Method for the intensive care unit.

g RBANS: Repeatable Battery for the Assessment of Neuropsychological Status.

h SF-36: 36-item Short-Form Health Survey.

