### Clinical Data Collection and Processing

A formal Data Monitoring Committee is not required for this study, as there are no interventions being tested and no anticipated risks to participants beyond standard clinical care. Therefore, no interim analyses or stopping guidelines are planned.

The study conduct will be monitored by the study physician and the research team according to standard operating procedures to ensure data quality and protocol adherence. Since there are no safety concerns beyond routine care, no additional independent monitoring is planned.

Clinical parameters are systematically documented and collected throughout the project. These parameters are exported from the routine medical documentation within the various subsystems of the electronic health records. On regular wards, this will be done through the Hospital Information System, and in ICUs, through the Patient Data Management System, capturing the entire course of patient treatment. The clinical data include vital parameters, medications, diagnoses, procedures, and laboratory values. Anesthesia documentation is supplemented by a digital Anesthesia Information Management System, which closely monitors all perioperative anesthesia parameters, including medication, vital signs, and ventilation parameters. Intraoperative electroencephalogram data, recorded during anesthesia depth monitoring, will also be captured.

These routinely collected data will be supplemented by explicitly requested variables to determine study end points, such as delirium scores. For this purpose, a study nurse will assess delirium preoperatively, upon transfer from the recovery room, and on the 5 subsequent postoperative days using the CAM, or CAM-ICU if the patient is transferred to the ICU. A learning effect from repeated testing is only to be expected in patients without delirium. Other outcome parameters include neuropsychological status measured by the Repeatable Battery for the Assessment of Neuropsychological Status, health-related quality of life assessed with the 36-item Short Form Health Survey, and mortality on the day of hospital discharge, as well as on days 30 and 90 after surgery.

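### Home use of cholinesterase inhibitors can confound the comparison of AChE and BChE activity between patients with and without POD, and the stated feature screen does not separate users

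*Protocol article*

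**What the plan says.** Blood Sampling and Analysis selects the two enzymes: "The activity of acetylcholinesterase and butyrylcholinesterase will be assessed using ELISA (enzyme-linked immunosorbent assay"). The same section puts their genes first among the methylation candidates studied for POD ("an analysis of candidate genes, such as ACHE, BCHE, CHRNA7, chemokines, and cytokines, will be conducted to investigate methylation processes associated with the occurrence of"). In Table 1 the row "AChE^c^ measurement" is ticked at nine time points: baseline, induction, intraoperative, recovery room and days 1 to 5.

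Textbox 1 (Patient Recruitment) has one drug criterion aimed at the cholinergic system, existing anticholinergic medication, and one cognitive criterion, severe dementia. It has none on cholinesterase inhibitors. The Introduction links cognition to the outcome: "Risk factors for POD include preoperative impaired cognitive and general health status".

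Integrative Data Analysis and AI Model Development names t tests and ANOVA, adjusted for multiple comparisons, as the way to pick candidate features. It names no covariate for that step. The medication profile is listed explicitly as an input only to the preoperative clinical model, which uses no blood sample.

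Drug exposure is recorded. In Clinical Data Collection and Processing, "The clinical data include vital parameters, medications, diagnoses, procedures, and laboratory values", and the anaesthesia system "closely monitors all perioperative anesthesia parameters, including medication, vital signs, and ventilation parameters". On neuromuscular block, the Methodology section says "if required, rocuronium for muscle relaxation" and names no reversal agent.

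**The concern.** A cholinesterase inhibitor acts on the enzyme being measured. If it is prescribed more often to patients with impaired cognition, and these patients develop POD more often, exposure is associated with both marker and outcome. That is confounding by indication. An unadjusted comparison of POD with no POD would then show an enzyme difference even if the enzyme had no relation to delirium.

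The eligibility rules leave this path open: they deal with one class of drug acting on the cholinergic system and not with the class that acts on the study's own analyte. Adjustment for multiplicity lowers each test's threshold but does not remove a systematic shift.

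The biomarker and mechanism aims are at stake. Significant findings go on to a knowledge base, targeted proteomics and mechanistic hypotheses. A validation cohort recruited under the same criteria could reproduce the same artefact.

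**Working it through.** The article gives no figure for inhibitor use, for enzyme levels or for a drug effect on the assay, so there is no stated figure to reproduce. The calculation below is an illustration.

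**Inputs from the article (Sample Size Considerations)**
- Expected incidence 24%, shown as 72 of 300, which leaves 228 without POD.
- Target of 100 POD cases with about 200 to 300 enrolled, so 100 versus 200 at the upper end. These two scenarios imply different incidences (24% and 33.3%) and are shown separately.

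**Assumed inputs, not in the documents**
- Share of home users p: 2% to 12%.
- Relative risk of POD in users, RR: 1.5 to 2.
- Shift D in the measured value among users: 0.5 to 2.5 SD.
- Within-group SD of 1 and no true link between enzyme and POD.

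**Formulas**, with overall incidence I
- Risk in non-users: r0 = I / (1 − p + p·RR).
- Share of users among cases: a = p·RR·r0 / I. Among controls: b = p·(1 − RR·r0) / (1 − I).
- Spurious difference: d = (a − b)·D.
- SE = √{[1 + D²a(1 − a)]/n1 + [1 + D²b(1 − b)]/n0}, and z = d/SE.
- Two-sided rejection rate at 0.05: Φ(z − 1.96) + Φ(−z − 1.96).

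**Worked example**: p = 8%, RR = 2, D = 2.5, I = 24%, 72 versus 228
- r0 = 0.24/1.08 = 0.222.
- a = 0.08 × 2 × 0.222/0.24 = 14.8%.
- b = 0.08 × (1 − 0.444)/0.76 = 5.8%.
- d = (0.148 − 0.058) × 2.5 = 0.22 SD, SE = 0.175, z = 1.28, rejection rate 25%.

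**Results, false-positive rate of a single test, RR = 2**

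| Shift D | Groups | p = 4% | p = 8% | p = 12% |
|---|---|---|---|---|
| 2.5 SD | 72 vs 228 | 12% | 25% | 38% |
| 1.5 SD | 72 vs 228 | 8% | 14% | 22% |
| 2.5 SD | 100 vs 200 | 16% | 37.5% | 57% |
| 1.5 SD | 100 vs 200 | 10% | 21% | 33% |
| 1 SD | 100 vs 200 | 7% | 13% | 19% |

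In the first row the spurious differences are 0.12, 0.22 and 0.31 SD.

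**Near-null cases, 72 versus 228**
- p = 2%, RR = 2, D = 1.5: 5.9%.
- p = 4%, RR = 1.5, D = 1.5: 5.8%.
- p = 8%, RR = 2, D = 0.5: 6.2%.

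**Second set of assumptions**, fixing use directly at 5% vs 2%, 10% vs 3% or 15% vs 5% in POD vs control, with D of 1 to 2 SD: the shift is 0.03 to 0.20 SD. The rejection rate is 5.5% to 23% with 100 versus 100 patients and 5.7% to 28% with 100 versus 200.

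If use is equal in both groups, or users are set aside, d = 0 and the rate returns to 5%. All rates are before the planned multiplicity adjustment.

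**The case against.** The strongest reply is that this belongs to the analysis plan. The article says that one exists, it is not shown, and covariate adjustment for a single marker is the kind of detail an article leaves out. This stands in part: the unseen plan may already deal with it. But the path arises from two choices fixed in the article, the marker and the eligibility criteria, and the screen the article does name would not close it.

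A reader might infer that the plan ignores drug exposure altogether. The documents do not support that. Medication is recorded on the ward, in intensive care and in theatre, the delirium risk score counts medication use, MMSE is taken at inclusion, and clinical and molecular data are to be combined. The t tests are a screening step before multivariable models.

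A reader might also infer that reversal of neuromuscular block contaminates the recovery-room sample. The Methodology section lists "the administration of propofol, sufentanil, and, if required, rocuronium for muscle relaxation, as well as maintenance with sevoflurane" and no reversal agent. That an inhibitor is given, and that its use differs by POD status, would both have to be assumed. With equal exposure there is no bias.

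Third, the size is insecure. Every drug-related input is assumed, and the article does not say whether its ELISA reading, described as activity, changes with inhibitor exposure. This stands.

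Finally, the models are declared exploratory and in need of external validation, and a drug-linked marker does less harm to pure prediction. That lowers the stakes without removing the bias from the biomarker aim.

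**Conclusion.** The point holds for home use. Inhibitor users with non-severe cognitive impairment are eligible, impaired cognition is a stated risk factor for POD, and the named screen would not separate a drug effect on AChE or BChE from an association with delirium.

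The size is unknown. Over the assumed ranges the single-test error goes from about the nominal 5% to 38% (72 versus 228) or 57% (100 versus 200). Low use or small shifts mostly give 5% to 10%. The conclusion rests on three assumptions outside the documents: that these drugs are taken more often by patients with impaired cognition, that users have a higher risk of POD, and that exposure moves the assay reading.

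It does not follow that an observed difference would be due entirely to the drug. That is a possibility, not a prediction. The perioperative part is conditional on an inhibitor appearing in the anaesthesia records. The exploratory biomarker and mechanism aims are affected more than prediction.

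**What to change.** 1. Derive a flag for home cholinesterase-inhibitor use from the medication data already recorded.
2. Report the comparison of AChE and BChE with POD in non-users, together with the whole-cohort result adjusted for the flag and for baseline MMSE.
3. State whether the ELISA reading is expected to change with inhibitor exposure.
4. For the recovery-room sample, flag any intraoperative cholinesterase inhibitor found in the anaesthesia record and adjust for it as a sensitivity analysis. Adjustment is better than dropping exposed patients, because exclusion could remove much of that sample if such use were common. If none is found, the step falls away.

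Fixing these rules before the cholinesterase values are compared with POD status keeps the choice independent of the result.

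The cost is two derived variables and a smaller sample for the non-user analyses only. At 2% to 12% use, 6 to 36 of 300 patients would be set aside (0.02 × 300 and 0.12 × 300). At 12% use and a relative risk of 2, about 15 of 72 cases would be among them (0.214 × 72), which is why the adjusted whole-cohort result should stand beside it. No change to eligibility or anaesthetic care is proposed.

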### Clinical Data Collection and Processing

A formal Data Monitoring Committee is not required for this study, as there are no interventions being tested and no anticipated risks to participants beyond standard clinical care. Therefore, no interim analyses or stopping guidelines are planned.

The study conduct will be monitored by the study physician and the research team according to standard operating procedures to ensure data quality and protocol adherence. Since there are no safety concerns beyond routine care, no additional independent monitoring is planned.

Clinical parameters are systematically documented and collected throughout the project. These parameters are exported from the routine medical documentation within the various subsystems of the electronic health records. On regular wards, this will be done through the Hospital Information System, and in ICUs, through the Patient Data Management System, capturing the entire course of patient treatment. The clinical data include vital parameters, medications, diagnoses, procedures, and laboratory values. Anesthesia documentation is supplemented by a digital Anesthesia Information Management System, which closely monitors all perioperative anesthesia parameters, including medication, vital signs, and ventilation parameters. Intraoperative electroencephalogram data, recorded during anesthesia depth monitoring, will also be captured.

These routinely collected data will be supplemented by explicitly requested variables to determine study end points, such as delirium scores. For this purpose, a study nurse will assess delirium preoperatively, upon transfer from the recovery room, and on the 5 subsequent postoperative days using the CAM, or CAM-ICU if the patient is transferred to the ICU. A learning effect from repeated testing is only to be expected in patients without delirium. Other outcome parameters include neuropsychological status measured by the Repeatable Battery for the Assessment of Neuropsychological Status, health-related quality of life assessed with the 36-item Short Form Health Survey, and mortality on the day of hospital discharge, as well as on days 30 and 90 after surgery.

These primary clinical and scientific data are then processed by a data scientist using a data integration pipeline to ensure that they are prepared for further analysis. This clinical data will be prepared for further analysis steps as outlined in Integrative Data Analysis and Development of a Delirium Prediction Model. To achieve this, an ETL (extract, transform, load) process will be developed. The aim is to automate this process so it can be utilized in subsequent research projects. A core dataset will be defined, representing comprehensive clinical parameters within a standardized data schema and unified semantics. This will be based on the OMOP CDM (Observational Medical Outcomes Partnership Common Data Model) standard from the Observational Health Data Sciences and Informatics initiative.

The OMOP CDM standard includes the representation of clinical content using standardized vocabularies, enabling the mapping of primary data from various data standards (eg, International Classification of Diseases, 10th Revision [ICD-10] and German Procedure Classification System [OPS]) and facilitating conversion to modern data ontologies such as SNOMED-CT (Systematized Nomenclature of Medicine—Clinical Terminology) and/or LOINC (Logical Observation Identifiers Names and Codes). Furthermore, OMOP CDM supports the eventual integration into the developing research data infrastructure of the Medical Faculty at Ruhr University Bochum, potentially using Health Level Seven Fast Healthcare Interoperability Resources (HL7 FHIR) profiles. This infrastructure constitutes the integration pathway for clinical deployment. Clinical input data (eg, demographics, vital signs, laboratory values, medications, and delirium assessments) are captured automatically from the Hospital Information System, Patient Data Management System, and Anesthesia Information Management System without additional manual data entry by clinical staff, and risk predictions are generated automatically within existing workflows at the point of care. For the preoperative clinical model, all input variables are documented as part of standard preanesthesia assessment, and no laboratory analyses are required, meaning a risk prediction is available immediately at the time of the outpatient consultation with no analytical turnaround time. For the integrative postoperative model, predictions are updated automatically as new data are entered into the electronic record, ensuring timely availability for clinical decision-making throughout the hospital stay.

The processed clinical data will then be combined with data from subsequent work packages to support the development of an artificial intelligence (AI) model. Individual deidentified participant data (including the data dictionary), statistical code, and any other materials will be accessible to authorized personnel of the AI Center.

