Given the limited sample size relative to the high-dimensional omics data, all predictive models are exploratory and hypothesis-generating. External validation in independent cohorts will be necessary to confirm predictive performance and clinical utility. Models trained on clinical variables alone will be benchmarked alongside multiomics models for exploratory comparison, reflecting potential applicability in settings where omics data are not routinely available.

The final operating threshold will be selected to prioritize either sensitivity (screening scenario) or specificity (confirmatory setting), as dictated by the clinical use case. Alongside the integrative models, versions limited to routinely available clinical variables will be trained and benchmarked to ensure bedside applicability where omics data are not regularly available. To interpret the resulting models, feature-attribution techniques such as SHAP (Shapley Additive Explanations) values will quantify and visualize each variable’s influence on the prediction, thereby generating mechanistic hypotheses about the molecular and functional pathways leading to POD. To clarify the clinical deployment strategy, the study is designed to yield 2 distinct and complementary model types. The first is a purely preoperative clinical model, trained exclusively on variables available at the preanesthesia outpatient clinic, specifically the DRAS, Mini-Mental State Examination score, age, comorbidities, surgical type, and medication profile. This model requires no blood sampling and can generate a risk prediction at the time of the outpatient consultation, typically days to weeks before surgery. This is the primary bedside instrument of the study and the relevant window for initiating preventive measures, including medication review and reduction of anticholinergic burden, sleep hygiene counseling, optimization of sensory aids, cognitive stimulation, and planning of early postoperative mobilization. The second is an integrative multimodal model incorporating longitudinal biomarker data from all 4 perioperative collection time points. This model serves a distinct purpose: continuous refinement of risk estimates throughout the hospital stay, enabling early detection of evolving POD in the postoperative period. Postoperative biomarker data are therefore not a prerequisite for preoperative risk stratification but an additional layer extending clinical utility into the postoperative setting.

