Future directions should focus on improving the interpretability of AI models, integrating them into clinical workflows, and considering ethical aspects. Collaborative efforts between data scientists, clinicians, and researchers are essential to validate AI-driven predictive models and ensure their successful application in clinical settings. By overcoming these challenges, AI has the potential to significantly improve the accuracy of POD prediction and facilitate personalized interventions, ultimately improving patient outcomes and reducing the burden of POD. With regard to cost-effectiveness, a formal health-economic analysis lies beyond the scope of this protocol study, but several considerations are relevant. First, the preoperative clinical model relies exclusively on routinely collected clinical data and requires no additional laboratory analyses, thereby incurring no additional diagnostic costs. Second, POD is associated with a well-documented economic burden, including prolonged hospitalization, higher rates of institutionalization, extended mechanical ventilation, and long-term cognitive decline. Targeted nonpharmacological prophylaxis initiated following early identification of high-risk patients has been shown in randomized trials to reduce POD incidence and shorten hospital stays, yielding downstream cost savings that are likely to outweigh the costs of screening. Third, the full proteomic and transcriptomic workup performed in this study is explicitly designed to identify a focused panel of high-yield biomarkers, which is anticipated to inform the development of targeted, lower-cost point-of-care assays for future routine clinical implementation, substantially reducing per-patient costs relative to the comprehensive analytical workup performed during the study phase.

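### The preoperative model is said to use only routine data, but one of its named inputs, the MMSE, is described only as a study-inclusion procedure

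*Protocol article*

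**What the plan says.** The section Integrative Data Analysis and AI Model Development presents the preoperative clinical model as the study's main bedside tool and lists its inputs: "specifically the DRAS, Mini-Mental State Examination score, age, comorbidities, surgical type, and medication profile".

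Three statements describe where the data for deployment come from:

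- Clinical Data Collection and Processing, on the preoperative model: "all input variables are documented as part of standard preanesthesia assessment, and no laboratory analyses are required".
- The same section, on clinical input data in general, which are to be taken from the hospital systems: "without additional manual data entry by clinical staff, and risk predictions are generated automatically within existing workflows at the point of care". Delirium assessments are among the examples given.
- Strengths and Limitations: "the preoperative clinical model relies exclusively on routinely collected clinical data and requires no additional laboratory analyses, thereby incurring no additional diagnostic costs".

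Two statements describe how some of these data are obtained in the study:

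- Methodology (text after Figure 1): at study inclusion, "cognitive status is assessed to ensure eligibility and to document baseline cognitive function", and for this purpose "a Mini-Mental State Examination and a Delirium Risk Assessment Score (DRAS) test are included as part of the consent process". On the DRAS it adds: "The DRAS is determined preoperatively in the preanesthesia clinic by evaluating patient-related factors such as age, comorbidities, type of surgery, and medication use".
- Clinical Data Collection and Processing, after describing the routine exports: "These routinely collected data will be supplemented by explicitly requested variables to determine study end points, such as delirium scores". A study nurse carries out these delirium assessments.

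**The concern.** A prediction model can be used only where its predictors are available, measured as they were when the model was built. If an input exists because patients joined the study, then in ordinary clinic use the model either cannot run as described or runs with that input missing. The discrimination and calibration reported would then belong to a different predictor set from the one deployed.

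The MMSE is the only one of the six inputs that directly tests cognition, and the Introduction names impaired preoperative cognition among the risk factors for delirium. It is therefore not an input to assume negligible. The statements on routine data and automatic capture support the article's case for bedside use, so their basis matters to a reader deciding whether the model could be adopted.

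**Working it through.** The point rests on no sample size, event count or performance figure, so there is nothing to recompute. The check sets the statements side by side.

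**1. Preoperative model, input by input**

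| Named input | How the article says it is obtained | Does this support the routine-data claim? |
|---|---|---|
| Age, comorbidities, surgical type, medication profile (4) | Ordinary content of a preanesthesia visit; diagnoses, procedures and medications are exported from the records | Yes |
| DRAS (1) | Named within the consent process, but also scored in the preanesthesia clinic from factors such as the four above | Ambiguous; probably computable from routine items |
| MMSE (1) | At study inclusion, within the consent process, for eligibility and baseline documentation | Only through the general claim itself |

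The count is 4 + 1 + 1 = 6. One input is described only as a study procedure and one is ambiguous. Table 1 has no row for either test, so it does not settle the matter.

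**2. Do the planned routine-variable versions cover this?** The modelling section plans versions limited to routinely available clinical variables, but it contrasts these with settings that lack omics data. The preoperative model's input list keeps the MMSE. No fit is described that removes a clinical input collected for the study.

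**3. Do the planned SHAP values cover it?** They would show how much the fitted model leans on the MMSE. They do not give the performance of a model refitted without it, because correlated inputs can take over part of its role.

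**4. Delirium assessments.** One part of Clinical Data Collection and Processing places them among inputs captured automatically from hospital systems. An earlier part of the same section sets delirium scores apart from routine data, as variables requested for the study and scored by a study nurse. Delirium assessments are not among the six preoperative inputs, so this bears on the integrative postoperative model, whose predictions are to update from the electronic record.

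**5. Size.** The article gives no rate of routine MMSE recording, no time or cost for the test, and no performance with and without it. The loss, if any, cannot be calculated from the article; the study's own data can measure it.

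**The case against.** The strongest reply is that being part of the consent process gives the timing of the test and does not place it outside standard care. Recruitment takes place in the same preanesthesia clinic, the modelling section treats the MMSE as available there, and the clinic may well record it for everyone. This stands: the article does not show that the MMSE is absent from routine care, so what is established is an inconsistency to resolve.

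Several stronger readings are tempting, and the article does not support them:

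- *The reported performance will not apply in routine use.* If the clinic gives the MMSE in the same way at deployment, performance can carry over. The risk arises only if the test is missing or measured differently.
- *The DRAS is also available only for study patients.* It is scored in the clinic from routine-type items, and all patients presenting there are screened against an eligibility threshold on it.
- *The study nurse's delirium scores undermine the preoperative model.* They are not inputs to it. The automatic-capture statement also speaks of entry by clinical staff, so a study nurse's scoring does not directly contradict that wording. The open question is who supplies the scores once the study nurse is gone.
- *Cognition is the leading risk factor, so the MMSE must carry most of the discrimination.* The Introduction lists it among several factors without ranking it, and excluding severe dementia may narrow the range of scores.
- *The no-cost claim is false.* That sentence is tied to the absence of laboratory analyses. A bedside test bears more on the claim of exclusively routine data.

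It can also be said that all models are declared exploratory and subject to external validation. That is true, but a validation cohort that also gave the MMSE for study purposes would leave routine-record performance unmeasured.

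**Conclusion.** The point holds for the MMSE. The article makes it an input of the main bedside model, claims that all inputs are standard and routinely collected, and describes the test itself only as a study-inclusion procedure. One of six named inputs is affected. The consequence is conditional: if the MMSE is not recorded routinely at this clinic, the reported performance may not describe the automatic, routine-data use claimed, by an amount that cannot be derived from the article.

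The mismatch over delirium assessments is a second, smaller point, confined to the integrative postoperative model.

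The verdict assumes that the six listed inputs are the complete set and that the DRAS can be computed from routine clinic items. Neither the sample size nor the planned validation is affected. The change is worth making because it is cheap and would show whether the routine-data claim can stand.

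**What to change.** 1. State whether the MMSE, and the DRAS, are recorded in the clinic's systems for patients outside the study.
2. Fit the preoperative model with and without the MMSE inside the same nested cross-validation, using the same folds, and report both with the difference. Keep the DRAS in both fits if it can be computed from routine clinic items; otherwise drop it from the routine version too.
3. Attach the routine-data and automatic-capture statements in Clinical Data Collection and Processing and in Strengths and Limitations to the version without the MMSE, unless routine recording outside the study is shown. For the version with it, say that the clinic visit must include the test.
4. Reconcile the two statements on delirium assessments in Clinical Data Collection and Processing, and say how those scores would reach the integrative postoperative model in ordinary use.

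The cost is one more model fit on data the study already collects, and some rewording. Recruitment is still open and data lock is still to come, so the second fit can be specified before the final data are in. The downside is that the routine-only figure may be less favourable.
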